## Abstract

*Background*. In the past, moxibustion has been widely used to treat endocrine system disorders, but evidence of its effectiveness is scarce at this point. The aim of this multicenter, randomized, controlled trial is to evaluate the efficacy and safety of treating menopausal obesity with moxibustion. *Methods/Design*. There are six centers taking part in this randomized, controlled, parallel trial. A total of 216 patients with menopausal obesity will be randomly divided into two equal groups: the “moxibustion for harmonization of Yin and Yang” group and the gentle moxibustion group. A 12-week study period with moxibustion will be preceded by a 1-week baseline, followed by a 12-week follow-up. We will conduct an interim analysis to determine whether or not the treatment is efficacious and safe after 216 participants have completed a 12-week treatment period. Evaluations will be conducted at weeks 0, 4, 8, 12, 18, and 24. The main outcome is waist circumference (WC), and the rate of WC reduction will be compared to the baseline. An intention-to-treat analysis will be performed with a two-sided *P* value of <0.05 considered significant. Participants who withdraw from the trial will be analyzed according to the intention-to-treat formula (ITT). *Discussion*. These results will be used to support selecting the right moxibustion prescription and guiding the improvement of clinical efficacy. This trial will provide convincing evidence of moxibustion's effectiveness and safety in the treatment of obesity by “moxibustion for harmonization of Yin and Yang,” which will be conducive to the promotion and clinical application of the theory of “moxibustion for harmonization of Yin and Yang.” *Trial Registration*. This trial is registered with Clinical Trials.gov: NCT04943705 (registered on June 27, 2021).

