### 2.2. Study Design

This will be a multicenter, randomized, controlled, two-arm clinical trial, where 216 participants will be randomized at a ratio of 1 : 1 to two groups (108 participants per group). There are six academic hospitals in China where this study will be carried out: Hubei Provincial Hospital of TCM, Shanxi Provincial Hospital of TCM, Shenzhen Baoan Hospital of TCM (Group), Xiamen Hospital of TCM, Jiangsu Provincial Hospital of TCM, and the First Affiliated Hospital of the Hunan University of TCM. A 12-week treatment phase plus a 12-week follow-up period make up the 24-week duration of this research. If they are qualified for the study, each participant is required to keep a diet and exercise diary for the whole research cycle. All participants will receive 12 weeks of individual treatments in two groups: the “moxibustion for harmonization of Yin and Yang” will be administered once every 1 week, 60 minutes each time; the gentle moxibustion will be administered 3 times a week, 20 minutes each time. Outcomes will be assessed at the beginning, at the conclusion, and during the follow-up period. The Standard Protocol Items: Recommendations for Intervention Trials (SPIRIT) [26] are utilized in the protocol, which is based on the Standards for Reporting Interventions in Clinical Trials of Acupuncture (STRICTA) [27](Additional file 1).  Figure 1 provides a summary of the trial's design.

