#### 2.8.1. Primary Outcome Measurement

Since waist circumference is the easiest and most practical indicator to quantify obesity; evaluations will be done at weeks 0, 4, 8, 12, 18, and 24 to compare the rate of waistline reduction with the baseline. The correct method for waist circumference is to check the horizontal length of the huckle center or the lowest point of the ribs and the middle line of the outer horizontal line of the iliac crest. In order to avoid the errors generated during the measurement process, the test is measured by a professional training doctor.

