### 2.11. Statistical Analysis

SAS 9.3 software will be used by an impartial statistician to analyze the data (SAS Institute Inc, Cary, NC). Any participant who completes the randomized stage and receives at least one intervention will be analyzed using a full analysis set (FAS), with missing data for the important outcomes interpolated with the last observation carried forward, in accordance with the intention-to-treat (ITT) analysis strategy. Multiple imputations will be used to deal with missing data. All statistical inspections were used for bilateral testing, and statistical significance will be determined at *P* < 0.05.

For the patient's missing data, it is assumed that the deletion data is randomly missing, the lacking value of the research main indicator is used for multiple filling methods, the stochastic missing deletion assumption of multiple filling is performed, and the stability test of the missing data filling results is carried out by using pattern mixture model (PMM). The measurement data is described by average ± standard deviation ($\bar{x}\pm S$), median, maximum, and minimum, and the counting data and grade data are described by cases and percentages. Intergroup comparison will select the analysis method according to the data distribution feature: the measurement data is used to test or nonparameter testing; the count data is used in*χ*^2^inspection or Fisher's exact probability method, and the grade data is used in the nonparameter test. Compared with the baseline value, the metering data is used in pair*T*inspection or nonparameter test, and counting materials use nonparameter test.

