### 2.13. Quality Control

The acupuncture, methodology, and statistics specialists examine and make revisions to the study protocol. A predetermined standard operating procedure will be used to teach the relevant employees. Through health education and prompt follow-up, patient compliance will be increased. If the subjects stop using moxibustion or depart from the procedure, the results will also be assessed by outcome assessors. This study will carry out a central randomization system to prevent bias in selection. At the same time, one of the most crucial strategies for preventing bias is the careful selection of inclusion and exclusion criteria, contributing to the objectivity of conclusions. A third-party blinded method will be applied to this study, namely, for assessing efficacy and safety by assessors who are not familiar with the group characteristics. To ensure the smooth progress of the study, all clinical researchers will be trained in the SOPs about moxibustion before the study begins to improve the consistency of researchers' and spectators' internal observations, in order to guarantee the validity of the conclusions. We will conduct sensitivity analyses in the per-protocol set. During this study, we will hold regular multicenter team meetings and go through routine checks to prevent center bias.

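### Waist reduction is to be compared between arms by an unadjusted test picked from the observed distribution; one pre-specified ANCOVA with baseline waist and centre would be sharper at no cost

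*Protocol article*

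**What the plan says.** Section 2.11 (Statistical Analysis) gives the rule for comparing the arms: "Intergroup comparison will select the analysis method according to the data distribution feature". For continuous variables it continues that "the measurement data is used to test or nonparameter testing". The clause is damaged, but the contrast with a nonparametric test makes a two-sample t test the natural reading. For change within an arm it says "Compared with the baseline value, the metering data is used in pair", followed by a t test or a nonparametric alternative. That is a before-after comparison, not a comparison of arms. The section names no model, covariate or centre term.

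The primary outcome in section 2.8.1 is waist circumference, assessed at weeks 0 to 24 to "compare the rate of waistline reduction with the baseline". The sample size in section 2.9 rests on mean improvement in cm: 6.15 (SD 1.56) against 3.94 (SD 1.14).

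On centres, the Abstract says "There are six centers taking part in this randomized, controlled, parallel trial", and section 2.13 says "we will hold regular multicenter team meetings and go through routine checks to prevent center bias". Section 2.5 describes central randomization and names no stratification factor.

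**The concern.** Three things are at stake.

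- **Precision.** Waist is measured in everyone at week 0 and should predict later waist well. A change score uses that information with a fixed slope of 1. ANCOVA estimates the slope and in large samples is never less precise. Centre may also explain some variance, because the treatment is applied by hand and the outcome is read from a tape at six hospitals.
- **Chance imbalance.** If one arm starts with larger waists by chance, a change score removes only part of the consequence. A fraction (1 − rho) of the baseline difference stays in the estimate.
- **What the result means.** A t test yields a mean difference in cm, which is the quantity behind the sample size. A rank test does not, unless a matching estimator is named, and none is. If the observed distribution decides between them, the form of the primary result is unknown until the data are seen. The rule also sits awkwardly with the multiple imputation in the same section, since standard pooling needs an estimate and standard error from each imputed dataset.

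**Working it through.** **Inputs from the protocol article.** Section 2.9: improvements 6.15 and 3.94 cm, SDs 1.56 and 1.14, one-sided alpha 0.025, power 80%, 96 evaluable and 108 randomized per arm.

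**Assumptions (not in the documents).** Baseline SD of waist s = 8 cm, the same SD at follow-up, and between-centre share of variance 1% to 10%.

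**Step 1: the plan's own figure.**
- Difference = 6.15 − 3.94 = 2.21 cm.
- Pooled change SD = sqrt((1.56² + 1.14²)/2) = 1.366 cm.
- n per arm = 2 × (1.960 + 0.842)² × 1.366²/2.21² ≈ 6, not 96.
- The standardized difference that 96 per arm detects with 80% power is 2.802 × sqrt(2/96) = 0.404. With 2.21 cm kept, the change SD would have to be 2.21/0.404 ≈ 5.47 cm.

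The mismatch is a separate matter. It counts here because it leaves two candidate change SDs, 1.37 and 5.47 cm.

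**Step 2: saving from baseline adjustment.** With equal SDs at both visits:
- change-score variance = 2s²(1 − rho)
- ANCOVA variance = s²(1 − rho²)
- ratio = (1 + rho)/2, so saving = (1 − rho)/2
- rho implied by a change SD d: rho = 1 − d²/(2s²)

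| Change SD d | rho at s = 8 | Saving at s = 8 | Saving at s = 6 | Saving at s = 10 |
|---|---|---|---|---|
| 1.37 cm (section 2.9) | 1 − 1.867/128 = 0.985 | 0.7% | 1.3% | 0.5% |
| 5.47 cm (reproduces 96) | 1 − 29.87/128 = 0.767 | 11.7% | 20.7% | 7.5% |

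Of 216 patients, 0.7% is about 2 and 11.7% about 25. In the second row, the same 80% power would need 96 × 0.883 ≈ 85 per arm. Equivalently, 96 per arm would have power Φ(2.802/sqrt(0.883) − 1.960) ≈ 85%. In the first row, power at 96 per arm is about 100% with or without adjustment.

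**Step 3: imbalance left in a change score.** One standard error of the baseline difference is 8 × sqrt(2/108) = 1.09 cm. The part that remains is (1 − rho) × 1.09:
- rho 0.985: 0.016 cm, or 0.7% of 2.21 cm
- rho 0.767: 0.25 cm, or about 11% of 2.21 cm

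**Step 4: centre.** If centres account for 1%, 5% or 10% of outcome variance, a centre term reduces the 96 per arm to 96, 92 or 87 for the same 80% power.

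**The case against.** **Baseline is not ignored.** A reader might infer from the missing covariate that baseline waist plays no part, or that raw week-12 values are to be compared, where adjustment would save a great deal. The documents do not support either. The outcome is reduction from baseline and the sample size uses improvement, so the fair comparator is a change or percent-change test.

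**The gain may be negligible.** One could assume rho of 0.7 to 0.9 and claim a saving of 5% to 15%. With an 8 cm SD, that implies change SDs of 6.2 to 3.6 cm, well above the stated 1.56 and 1.14. On the stated SDs the saving is under 1%. This objection stands in part: those SDs do not yield 96 per arm, so they cannot settle the matter. Nor does the 5.47 cm figure. The 96 could also come from a smaller difference (about 0.55 cm) or an unstated superiority margin (about 1.66 cm) with the SDs unchanged.

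**The test is not invalid.** A reader might infer a biased comparison or an inflated error rate. Under randomization the unadjusted comparison is valid on average. The loss is of precision and of protection in the particular sample drawn.

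**Blinding softens the test choice.** Section 2.6 keeps the statistician blind to allocation, which limits opportunistic selection. It does not fix which effect measure is reported.

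**This is a condensed article.** Covariates are often left to an analysis plan, and section 2.11 does not forbid them. But it does state a rule for choosing the between-arm method, and that rule is the weakness.

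**Centre procedures exist.** Trained measurers (2.8.1), thermometer control in one arm (2.7.2) and SOP training (2.13) should reduce centre differences. The documents give no figure for what remains.

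**Conclusion.** The point holds as an improvement to a stated method, not as a flaw that invalidates the trial. The plan lets the distribution choose between a mean-based and a rank-based comparison, with neither baseline waist nor centre as a covariate.

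The direction of the gain from adjustment is clear but its size is not. It is about 0.7% of the variance on the SDs in section 2.9, and about 12% if the change SD is near 5.5 cm. Both figures rest on an assumed 8 cm baseline SD, equal SDs at the two visits and an outcome analysed as a change in cm. A percent-change analysis would not follow the formula exactly. The centre gain of 1% to 10% is simply the assumed range.

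The open question of what the primary result will be, a mean difference or a rank statement, does not depend on any of these assumptions.

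**What to change.** Before unblinding, replace the distribution-based rule for the primary outcome with one analysis that applies whatever the distribution looks like: ANCOVA of waist circumference at the designated primary time point on treatment, baseline waist and centre. A repeated-measures model over the visits with the same terms would also serve. Sections 2.8.1 and 2.11 list several visits without singling one out, so the time point must be named too; week 12, the end of treatment, is one example. Report the adjusted difference in cm with a 95% CI, which matches the scale of the sample size. Keep the rank test as a sensitivity analysis only.

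The cost is analysis wording. Week-0 waist is already scheduled for every participant and the treating centre is known, so no new data, visits or patients are needed.

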### 2.12. Safety Assessment

Vital signs and adverse events will be considered in the moxibustion safety evaluation. Prior to randomization and after therapy, a general physical examination using safety indicators such as blood pressure, heart rate, respiration, pulse, and body temperature will be performed. Aside from that, the frequency of adverse events, including moxibustion burns, blistering, dizziness, ulceration, infection, local abscess, irregular vaginal bleeding, fatigue, allergies, and anorexia will be meticulously recorded in the CRFs and monitored by the Ethics Committees.

### 2.13. Quality Control

The acupuncture, methodology, and statistics specialists examine and make revisions to the study protocol. A predetermined standard operating procedure will be used to teach the relevant employees. Through health education and prompt follow-up, patient compliance will be increased. If the subjects stop using moxibustion or depart from the procedure, the results will also be assessed by outcome assessors. This study will carry out a central randomization system to prevent bias in selection. At the same time, one of the most crucial strategies for preventing bias is the careful selection of inclusion and exclusion criteria, contributing to the objectivity of conclusions. A third-party blinded method will be applied to this study, namely, for assessing efficacy and safety by assessors who are not familiar with the group characteristics. To ensure the smooth progress of the study, all clinical researchers will be trained in the SOPs about moxibustion before the study begins to improve the consistency of researchers' and spectators' internal observations, in order to guarantee the validity of the conclusions. We will conduct sensitivity analyses in the per-protocol set. During this study, we will hold regular multicenter team meetings and go through routine checks to prevent center bias.

## 3. Discussion

The NCD risk factor collaboration [33] has shown that obesity is a significant worldwide health problem with a rise in prevalence from 3.1% in 2014 to 8.1% in 2018 [34]. It is estimated that 85 million Chinese adults aged 18–69 were obese in 2018 [35]. At present, the research on the treatment of obesity at domestic and abroad levels is mainly concentrated on acupuncture therapy, electroacupuncture, acupoint embedding, etc., with less research on moxibustion [36, 37]. Moxibustion, which comes in a variety of forms and is one of Traditional Chinese medicine's external therapeutic modalities, has been proved to be useful in the management of obesity [38–41], but it is considered to be a complementary therapy to acupuncture, which is usually used in combination with other therapeutic methods in clinical practice, resulting in the superiority of moxibustion being not fully realized. So far, few clinical trials have been conducted to confirm the efficacy and safety of moxibustion therapies for menopausal obesity. This is the first randomized controlled trial focusing on the variations in the effectiveness of “moxibustion for harmonization of Yin and Yang” compared to the gentle moxibustion for treating menopausal obesity. The outcomes will present evidence for better clinical effectiveness and prescription choice for moxibustion. Additionally, the outcomes of this experiment will be utilized to verify the safety and efficacy of the “moxibustion for harmonization of Yin and Yang” in regard to menopausal obesity treatment and provide high-level evidence-based evidence supporting the use of “moxibustion for harmonization of Yin and Yang” in the therapeutic treatment of menopausal obesity.

As stated by TCM's fundamental theory, the main causes of menopausal obesity are gradual failure of kidney qi, exhaustion of heavenly tenth, and Yin-Yang disharmony. The “moxibustion for harmonization of Yin and Yang” has the capacity to warm Yang and dredge collateral vessels, strengthen the root and reinforce deficiency, and mediate Yin and Yang; its thoughts originated from the theory of mutual rooting of Yin and Yang in classics of traditional Chinese medicine “Huangdi Neijing,” which is a detriment to yang affects yin and detriment to yin affects yang. When conducting syndrome differentiation and determining remedies, it pays close attention to the surroundings, individual constitution, and climatic and seasonal variables. By tonifying the pattern of dual deficiency of qi and blood, as well as Yin and Yang, eliminating the pathogenic factors of dampness and cold, the body functions will be in a state of Yin and Yang coordination and harmony. Hence, this study will select Shenque (RN8) and Mingmen (DU4) on the “moxibustion for harmonization of Yin and Yang” and Zhongwan (RN12), Guanyuan (RN4), and Sanyinjiao (SP6) on the gentle moxibustion because of the following reasons: (1) these acupoints have been demonstrated to be effective in accelerating metabolism and alleviating menopausal symptoms [25], (2) the gentle moxibustion candidate refers to the unified use of national Chinese medicine colleges, and the 13th five textbooks published by China Traditional Chinese Medicine “Acupuncture and Moxibustion Therapy” have pre- and postmenopausal symptoms and obesity-related prescriptions, and (3) one of the acupoints chosen is on the Yang side of the waist, the other is on the Yin side of the abdomen, and the two acupoints are located in the middle of the human body, reflecting the concept of “moxibustion for harmonization of Yin and Yang.”

From the following three perspectives, the efficacy evaluation will be carried out: obesity-related indicators, menopausal and obesity symptoms, and blood biological indicators. Waist circumference is a simple and important anthropometric measure of total and intra-abdominal body fat that the National Heart, Lung, and Blood Institute recommends as an indication of obesity in adults for the diagnosis, assessment, and treatment of overweight and obesity [42, 43]. Therefore, the primary outcome will be measured using the WC, which is valid, trustworthy, intuitive, and more accurate than the BMI in reflecting body adiposity [44]. At the same time, the obesity-related indicators (BMI, WG, HC, WHR, F%), obesity and menopause scale assessment (TCM clinical syndrome scores, modified Kupperman score, IWQOL-Lite, SF-36), and the changes in blood biochemical indicators (TC, TG, LDL-C, HDL-C, E2, FSH) will be assessed before and after therapy in this experiment as secondary outcomes. Patients with menopausal obesity have more serious symptoms and disturbed hormone levels [45]. Hence, IWQOL-LITE and SF-36 will be performed to assess symptoms and overall health of obesity [46, 47]. The Modified Kupperman score will be performed to identify patients with menopausal symptoms [48], and E2, and FSH will be used to assess the hormone levels in menopausal patients [49].

In conclusion, this multicenter, randomized, parallel, and controlled trial will evaluate the viability and superiority of “moxibustion for harmonization of Yin and Yang” and gentle moxibustion, as well as the efficacy and safety of various types of moxibustion treatments for menopausal obesity. It will also enhance the standardization of moxibustion for menopausal obesity and, to a greater extent, provide a clinical foundation for treatments, thereby better playing the role of moxibustion in disease treatment and health care.

## Figures and Tables

**Figure 1 fig1:**
[figure not shown]
Flow chart.

**Figure 2 fig2:**
[figure not shown]
Locations of acupoints in the “moxibustion for harmonization of Yin and Yang” group.

**Figure 3 fig3:**
[figure not shown]
Locations of acupoints in the gentle moxibustion group.

**Figure 4 fig4:**
[figure not shown]
Study schedule. IWQOL-Lite, the impact of weight on quality of life questionnaire; SF-36, the MOS item short from health survey; TCM, Traditional Chinese Medicine.

## Data Availability

Since no datasets were created or examined for this research, data sharing is not applicable.

## Abbreviations

WC: Waist circumference
WG: Weight
F%: Body fat percentage
BMI: Body mass index
HC: Hip circumference
WHR: Waist to hip ratio
ITT: Intention-to-treat
IWQOL-Lite: Impact of Weight on Quality of Life Questionnaire
SF-36: MOS item short from health survey
TC: Cholesterol
TG: Triglycerides
LDL-C: Low-density lipoprotein
HDL-C: High-density lipoprotein
E2: Estradiol
FSH: Serum follicle-forming hormone
STRICTA: Standards for reporting interventions for controlled trials of acupuncture
SPIRIT: Standard protocol items: recommendations for intervention trials
TCM: Traditional Chinese medicine.
